### Measures

Measures for this study are brief researcher-created surveys to measure song preference, expectation, and helpfulness for each song (see Multimedia Appendix 1). These measures were chosen to understand user preference in order to build a KE ML model and user personas for aims 1 and 2. These same measures will again be collected in a smaller sample for aim 3 to assess the acceptability of the ML-based music recommendations. Web-based surveys were developed by [name] and tested for usability and technical functionality by [name] and [name] prior to participant recruitment. Participants will be asked to answer each question for each song. Questions are 5-point Likert scales to measure song preference (strongly dislike to strongly like), sentiment (very sad to very happy), expectation for hearing that particular song for the goal of reducing depression (strongly disagree to strongly agree), and helpfulness (eg, “Would this song be helpful in making you feel better if you were very sad?”; strongly disagree to strongly agree). Participants will also be asked to assess their mood (eg, “How depressed are you?”) and engagement in daily activities prior to and directly following their survey on an 11-point Likert scale (0-10). Participant demographics will also be collected excluding directly identifying information that would link survey responses to participants.

Zip codes will be collected to verify geographical residence (rural, urban, or suburban) in order to build specific user personas tailored to each group (aim 1). After verification, only the first 3 digits of the zip code will be stored for each participant, and the digits will be changed to 000 in instances for which the zip codes contain less than 20,000 people.

Bot detection for survey entries based on reCAPTCHA was used, and any duplicate survey entries based on Prolific IDs were removed. Prolific uses participants’ email address and phone number to verify participants and IP address detection to ensure participants do not participate in studies more than once. There were an average number of 6.5 items per page with 8 total pages. All questions required an answer in order to submit the survey. Demographic questions included a “none of the above” or “prefer not to say” option, while music preference questions required a response on a 5-point Likert scale.

### Music Metadata

Each song in the SingFit catalog has been tagged with metadata for dozens of different parameters. Musical metadata include linguistic syntax and semantics (assessed with text analysis software), tempo and key (assessed using song analyzer software), genre, popularity, arousal, and others. The full list of metadata is proprietary to Musical Health Technologies but encompasses a wide range of cognitive and affective factors associated with known therapeutic benefits. These metadata will be used to understand the musical factors associated with user preference and clinical factors related to improvement in depressed mood. Music metadata is used in SingFit’s current song recommendation algorithms and will be used in knowledge graphs for comparing various KE model architectures during phase 1.

### Phase 2: Machine Learning Model Implementation and Evaluation

Music recommendation is an active area of research within the information retrieval community, with researchers facing unique challenges, such as data sparsity, complexity in evaluation, and personalization for cultural and situational awareness. The cold start problem, a lack of historical information for making decisions about new users or items, is a common issue across many recommendation systems that persists in the music domain [36,37]. Recent work has found promising results by using neural network models and incorporating metadata features such as song artist or genre with user interaction data to form a collaborative knowledge graph [37,38]. In particular, users, songs, and metadata categories are treated as nodes in a graph. Connecting edges represent semantic meaning, like a song belonging to a genre or a user favoriting a song. Neural network–based approaches like DeepWalk can be used for learning latent representations of the graph’s nodes in vector space [37,39]. At recommendation time, a song is compared to others in vector space, returning the most similar songs to the end user. This approach will allow the system to make recommendations based on the preferences of similar users in conjunction with shared music metadata and clinical features to maximize the relevance of recommendations.

The modeling architecture will largely follow Bertram et al [37] for creating knowledge graph embeddings of songs and relevant metadata features of both users and songs. Authors LD and VP will conduct explorations to vary the metadata features included in the knowledge graph and tune hyperparameters of the DeepWalk model. This will allow for thorough exploration of feature selection and model architecture choices, with the best performing modeling pipeline deployed for user testing. Models and data processing will be implemented in Python (Python Software Foundation) with widely used ML libraries, *scikit-learn* and *pytorch*, and support for graph structures with *pytorch-geometric* and *networkx*. The algorithms will be developed in collaboration with the data core at the University of Massachusetts Center for Data Science and the Massachusetts AI and Technology Center.

The data will be split into training, validation, and testing sets by user using 5-fold cross-validation. This will balance training and evaluation variances and allow for more efficient use of the relatively sparse data compared to using a single data split for training, validation, and testing sets. Splitting data at the user-level will simulate the cold start problem in our experiments. The model with the best average performance across the 3 test sets will be retrained on the entire dataset, a standard practice in ML. Baseline performance will be measured using a purely random recommendation system and a content-based learning-to-rank approach that relies solely on metadata features. These baseline benchmarks will help gauge the added benefit of more complex neural network recommendation algorithms.

Because clinical features may be in tension with musical preferences or musical features, multiple metrics are needed in order to understand the trade-off being made by the recommendation algorithm. The metrics that will be used to evaluate performance are root mean square error, normalized discounted cumulative gain, and a user-reported satisfaction score [36]. Root mean square error will be used to evaluate the error between the recommendation system’s estimated satisfaction score and the user’s true satisfaction score to ensure that it can accurately predict the user’s label of the song. Normalized discounted cumulative gain, a ranking quality metric, will be used on the songs recommended by the system to ensure that the test data songs are being recommended in an order equivalent to their user-preferred ranking. As part of further testing, a sample of users will be given a set of playlists recommended by the system and asked to answer the survey questions from phase 1. By comparing the satisfaction scores across phases, a comparison can be made as to the direct effects on the listener of the songs recommended.

For Aim 3, the goal is to develop a ML model with ≥80% accuracy in creating individualized therapeutic music playlists and achieve a user acceptability score of 85% or higher among rural-residing older adult users. Using the same survey questions from phase 1 (see Multimedia Appendix 1), the user acceptability score will be based on the average ratings for questions regarding the overall preference, relevance, and perceived benefit of the playlists. An a priori power analysis was conducted using G*Power version 3.1 [40] to determine the required sample size for a 1-sample *t* test for aim 3. The goal of the analysis was to detect a mean acceptability score significantly greater than 4.25 (indicating 85% acceptability), with a margin of error of 0.2 and an estimated SD of 1.2. Assuming a medium effect size (d=0.30), an α level of .05, and a desired power of 0.80, the analysis revealed that a minimum of 139 participants would be needed to ensure adequate statistical power.

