**Objective:**

This protocol aims to develop an intelligent recommendation system capable of identifying the optimal therapeutic music components to elicit engagement and resonate with diverse rural-residing older adults at risk for AD. Aim 1 is to develop culturally inclusive user personas for rural-residing older adults to understand their goals and challenges for music-based digital health intervention. Aim 2 is to develop knowledge embedding–based machine learning (ML) models that use music metadata and survey response data to identify optimal therapeutic music components for enhancing engagement and emotional resonance for depression among rural-residing older adults at risk for AD. Aim 3 is to assess acceptability for personalized therapeutic music sessions and ML-based music recommendations with a separate sample.

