### Phase 1: Data Collection and Preprocessing

In phase 1, web-based survey data will be collected from up to 1000 older adults. Participants will be instructed to sing along to a playlist designed to reduce mood symptoms associated with depression. This goal was selected because depression is known to significantly increase the likelihood of AD and accelerate cognitive decline [32]. Participants will receive 5 songs randomly chosen from a set of songs based on age and musical arousal—2 factors known to be associated with mood and relevance to older adults. Songs will be selected based on participants’ “reminiscence bump” [24] and will use the iso principle to modulate from low arousal to moderate arousal [33,34]. In past studies of the musical “reminiscence bump,” the strongest associations and familiarity with music was found to be between the ages of 15-24 years [25,35]. SingFit’s music selections are chosen from participants’ adolescence and young adulthood to ensure familiarity and narrative memory associations with the music. The iso principle gradually shifts the music from matching the participant’s emotional state (eg, sad) to their desired state (eg, calm). In phase 1, songs with high arousal were not included in order to modulate arousal and affect gradually for a depression playlist in keeping with the iso principle. Surveys will use 5-point Likert scales to measure song familiarity, perceived benefit, sentiment, relevance, and preference for each song, which will be analyzed in conjunction with music metadata (described below) to better understand musical factors associated with mood symptoms of depression. Participants will receive an open survey link to the Qualtrics survey and either listen or sing along to each song while completing survey questions for each song (ie, song preference or sentiment).

For the development of user personas and the ML model (aims 1 and 2), the planned sample size of 1000 participants was determined following deliberation with the study’s data consultants to balance feasibility and analytical utility within the scope of this pilot project. This sample was identified as the minimum viable cohort necessary to support adequate model training, validation, and initial testing of the recommender system.

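### Splitting by user alone simulates cold start for new users but not for new songs, and cannot by itself support Aim 2's conclusion about musical components

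*Protocol article*

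**What the plan says.** All places are in the protocol article.

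- **Split.** Phase 2 (Machine Learning Model Implementation and Evaluation): "The data will be split into training, validation, and testing sets by user using 5-fold cross-validation". The stated purpose follows: "Splitting data at the user-level will simulate the cold start problem in our experiments". No split by song appears anywhere.
- **Definition.** The same section describes the problem as "a lack of historical information for making decisions about new users or items".
- **Model and comparators.** Users, songs and metadata categories are all nodes in the knowledge graph. The plan is to vary the metadata features and deploy the best pipeline. Comparators are a random recommender and a ranker that uses metadata only.
- **Target.** The abstract's Objective has Aim 2 "identify optimal therapeutic music components for enhancing engagement and emotional resonance for depression". The Music Metadata section says the tags will be used to understand which musical factors go with preference and mood improvement.
- **Data.** Phase 1 (Data Collection and Preprocessing): "web-based survey data will be collected from up to 1000 older adults", each receiving 5 songs drawn at random from a set defined by age and arousal. In that phase "songs with high arousal were not included".
- **Later test.** A separate sample of 200 participants rates sets generated by the system.

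**The concern.** The definition has two parts, but the split addresses one and the sentence about it carries no limit. A held-out user is new to the model. The songs that user rated are in general not new, because training users rated them too.

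This matters most for Aim 2. Components vary between songs, not between ratings of one song, so the song is the independent unit for a statement about components. If some songs are liked more than others for reasons unrelated to any tag, a model with song nodes carries that liking over to new users. A model with many tags can do part of the same, because enough tags taken together come close to labelling individual songs. Good RMSE or NDCG could then be reported as evidence that components were identified, or that cold start was handled in general. Feature selection is exposed in the same way, since the pipeline to deploy is chosen on this split.

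**Working it through.** The plan gives no figure to reproduce here, so the check has two parts: how far songs overlap between training and test, and what that overlap can produce when no component matters.

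**1. Overlap.** Inputs from the document: 1000 users, 5 songs each, 5-fold split by user. Assumed: pool size K, and 600 training users (if a validation fifth is set aside) or 800 (if not). With 5 distinct songs drawn at random per user, the chance that a test song has no training rating is (1 − 5/K)^n.

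| K | n = 600 | n = 800 |
|---|---|---|
| 300 | 0.004% | 0.0001% |
| 500 | 0.24% | 0.03% |
| 1000 | 4.9% | 1.8% |
| 2000 | 22% | 13% |
| 3000 | 37% | 26% |

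Up to about 300 songs the overlap is practically complete, and at 500 nearly so. In pools of 1000 or more some test songs are unrated in training, but by chance, and the plan does not score them separately.

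**2. Apparent performance when no component matters.** Assumed: song SD 0.5, user SD 0.5, residual SD 0.9, all metadata effects zero, 800 training users. The outcome is the share of a new user's song pairs put in the right order (50% is chance).

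For continuous ratings a closed form is available. The user effect cancels within a user, so perfect knowledge of song effects gives a correlation with the observed difference of 0.5/√(0.25 + 0.81) = 0.486. The ceiling is therefore 0.5 + arcsin(0.486)/π = 66.1%.

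Song effects are estimated from m = 4000/K training ratings each, with reliability factor r = √(0.25/(0.25 + 1.06/m)), where 1.06 = 0.25 + 0.81:

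- K = 100: m = 40, r = 0.951, 0.5 + arcsin(0.486 × 0.951)/π = 65%.
- K = 300: m = 13.3, r = 0.871, giving 64%.
- K = 600: m = 6.7, r = 0.782, giving 62%.

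A regression on p features without true effect recovers song effects with a correlation of about r × √(p/K). Inserting this in place of r gives, for K = 100, 300 and 600, about 55%, 52% and 52% with p = 10, and 59%, 55% and 53% with p = 40.

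The study uses 5-point ratings, which tie often. Simulating these (mean 3.5 assumed) and dropping tied pairs gives:

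| Model and split | K = 100 | K = 300 | K = 600 |
|---|---|---|---|
| Song identity, user split | 69% | 67% | 65% |
| 40 null features, user split | 62% | 56% | 54% |
| 10 null features, user split | 55% | 53% | 51% |
| 10 or 40 null features, songs held out | about 50% | about 50% | about 50% |

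Repeat runs differ by up to about one percentage point. Dropping ties is what takes 69% and 67% above the 66.1% ceiling for continuous ratings, so the scoring convention has to be read with the figures.

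**The case against.** The strongest reply is that the user split fits the intended use: recommending to new users from an existing tagged catalogue. Aim 2 does not expressly claim to extend to unrated songs. That stands, and the split should stay.

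The plan also has safeguards. The metadata-only baseline has no song node, so a wide gap between it and the graph model would show how much performance rests on song identity. The planned variation of metadata features is close to an ablation. With few features and a large pool the protection is good: 10 null features and 600 songs give 51%. It is only partial otherwise, because the baseline is scored under the same user split. The catalogue carries dozens of tags, and 40 null features give 62% with 100 songs.

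Two stronger readings are tempting, and the document supports neither.

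- A reader might infer that every song is in both training and test data. That depends on the pool size, which is not given, and it fails for pools of 1000 or more. What can be said is that no song is held out by design.
- A reader might infer that the system is never tested on an unrated song. The 200-person test neither provides for nor excludes such songs. What can be said is that no separate evaluation of them is stated.

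Leaving high-arousal songs out of phase 1 is disclosed and explained, and no claim about them is made. It bears only on how far component conclusions can reach.

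**Conclusion.** The point holds in a limited form. By the protocol's own definition the user split simulates cold start for new users only, so the sentence claims too much. For Aim 2, performance under that split is not clean evidence about components, and the metadata-only baseline removes the ambiguity only in part.

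In the illustration, metadata with no true effect gains between 1 percentage point over chance (10 features, 600 songs) and 12 points (40 features, 100 songs). Song identity alone gains 15 to 19 points, or 12 to 15 with continuous ratings. These sizes rest on assumed variances, feature counts and pool sizes. They show the mechanism and its range and do not predict this study's results. The mismatch between definition and split rests on the text alone. This is a worthwhile, cheap improvement and does not invalidate the new-user evaluation.

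**What to change.** 1. Keep the user split for new-user performance, together with the metadata-only baseline and the planned feature variation.
2. Add a cross-validation that holds out songs. For held-out songs, remove all user edges and ratings and keep only metadata edges. Two or three song folds leave each user on average 5/2 = 2.5 or 5/3 = 1.7 unseen songs to order.
3. Under that split, score the metadata-only baseline, then drop one metadata group at a time and report the change in held-out performance. Base the Aim 2 statement about components on this result.
4. In the Phase 2 section, limit the cold-start sentence to new users unless the song-held-out result supports more. Limit component conclusions to the arousal range rated in phase 1.
5. Report the size of the song pool and the number of ratings per song, so that readers can judge the overlap.

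The cost is extra computation on data already collected and a few sentences. The article describes analysis as still under way, so the change fits. The downside is that song-held-out performance will probably be lower than under the user split.

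### The final model is chosen on the test sets, and the stated 3 test sets do not fit 5-fold cross-validation, so the phase 1 cross-validated performance and gain over baselines will be somewhat optimistic

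*Protocol article*

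**What the plan says.** All of this is in the Protocol article, Methods, mostly under Phase 2: Machine Learning Model Implementation and Evaluation.

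- **Scheme:** "The data will be split into training, validation, and testing sets by user using 5-fold cross-validation".
- **Selection rule:** "The model with the best average performance across the 3 test sets will be retrained on the entire dataset". The sentence adds that this is standard practice.
- **Search:** metadata features are to be varied and hyperparameters tuned. "This will allow for thorough exploration of feature selection and model architecture choices, with the best performing modeling pipeline deployed for user testing".
- **Baselines:** "Baseline performance will be measured using a purely random recommendation system and a content-based learning-to-rank approach that relies solely on metadata features". Their purpose follows: "These baseline benchmarks will help gauge the added benefit of more complex neural network recommendation algorithms".
- **Ranking metric:** NDCG is to be computed on test data, "to ensure that the test data songs are being recommended in an order equivalent to their user-preferred ranking".
- **Data available** (Phase 1: Data Collection and Preprocessing): "In phase 1, web-based survey data will be collected from up to 1000 older adults".
- **Later test:** the Abstract describes a separate sample of 200 participants and names RMSE, NDCG and mean acceptability. No baseline recommender is described for that sample.

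**The concern.** There are two separate faults.

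The first is a contradiction of count. The article names five folds and then averages over three test sets, so it is unclear which users enter the score that decides the winner.

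The second is the selection rule. A test set gives an honest estimate only if it played no part in choosing the model. Here the model with the best test score wins, and the test folds are also the place where performance is measured. Part of the winner's score is then luck on those particular users. The baselines are not picked as the best of many, so the comparison favours the complex model. What is at stake is whether the phase 1 results show that the knowledge-embedding approach adds anything to a simpler recommender built on metadata alone.

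**Working it through.** **1. The count.** With up to 1000 users and 5 folds, each test fold holds 1000 / 5 = 200 users, and the five rotations give five test sets covering all 1000. If 3 is read as the three-way partition (training, validation, test), there is still one test set per rotation, so five in all. The figure of 3 cannot be reproduced from a single 5-fold scheme. If it were literal, 3 × 200 = 600 users would be scored and 400 would not, and the standard error would rise by √(1000/600) = √(5/3) = 1.29.

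**2. The selection rule.** The article describes a search over features, hyperparameters and architectures, names validation sets, and then ties the choice of final model to average test performance. It describes no nested loop and no phase 1 test set held back from the choice. Retraining the chosen model on all data is indeed ordinary practice, but that does not justify making the choice on test scores.

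**3. Size of the optimism.** The article gives none of the inputs except the number of users, so these are assumptions: K candidates of equal true performance, per-user NDCG SD 0.10 to 0.15, and correlation ρ between candidates' scores of 0 to 0.9. With E[max_K] the expected maximum of K standard normal variables,

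optimism = E[max_K] × SD × √((1 − ρ) / n).

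For n = 1000:

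| K | E[max_K] | SD 0.10, ρ 0.9 | SD 0.15, ρ 0.5 | SD 0.15, ρ 0 |
|---|---|---|---|---|
| 3 | 0.85 | 0.0008 | 0.0028 | 0.0040 |
| 5 | 1.16 | 0.0012 | 0.0039 | 0.0055 |
| 20 | 1.86 | 0.0019 | 0.0063 | 0.0088 |
| 50 | 2.25 | 0.0023 | 0.0075 | 0.0107 |
| 200 | 2.74 | 0.0027 | 0.0092 | 0.0130 |

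The largest entry, for example, is 2.74 × 0.15 × √(1/1000) = 0.0130. The range is about 0.001 to 0.013. With only 600 users scored it would be about 0.001 to 0.017.

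**4. Effect on the comparison with a baseline.** This is a simulation of 10,000 replicates with SD 0.15, ρ 0.5, 1000 users, and a baseline truly as good as every candidate. The standard error of the difference is 0.15 × √(2 × 0.5 / 1000) = 0.0047, so a nominal one-sided 5% comparison declares a gain above 1.645 × 0.0047 = 0.0078.

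| K | Mean false gain, chosen on test folds | Gain declared, chosen on test folds | Gain declared, chosen on independent validation data |
|---|---|---|---|
| 2 | 0.0019 | 9% | 5.1% |
| 5 | 0.0039 | 17% | 5.3% |
| 20 | 0.0063 | 34% | 4.8% |
| 50 | 0.0076 | 48% | 4.9% |
| 100 | 0.0084 | 57% | 4.8% |

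With validation-based selection the mean false gain is zero to within 0.0001 at every K.

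**The case against.** The strongest reply is that a condensed article need not set out the tuning loop. It names validation sets, whose usual role is tuning, and it does not say on which data hyperparameters are tuned. A fair reading is that tuning uses validation users and only a few finished models meet on the test folds. The bias would then sit near the K = 2 to 5 rows. That stands as a limit on size. It does not remove the point, because the article states the final selection rule and that rule uses test scores.

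It is also true that the article announces no test or threshold for the gain over baselines, calls the project a pilot, and warns under Limitations that 1000 participants is small for training such models. The baselines are nevertheless its stated means of judging added benefit.

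Four stronger readings might be inferred, and the document does not support them:

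- *All reported performance is optimistic.* It is not. Acceptability, and any RMSE or NDCG computed in the separate sample of 200, come from users who played no part in the selection.
- *The 3-versus-5 mismatch causes the optimism.* It does not. The optimism comes from selecting on test data and would be there with all five folds.
- *Two folds, 400 users, are discarded.* This follows only if 3 is literal. A miscount is at least as likely.
- *Models without skill would almost always appear to beat random recommendation.* A simulation with 50 independent no-skill pipelines does put the best of them ahead of one random ranking in 99% of runs. But exchangeability alone gives 50/51 = 98%. The figure counts only the sign of the difference, and both the 50 candidates and their independence are assumed.

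**Conclusion.** The point holds, confined to the phase 1 cross-validated figures. The fold count is an internal contradiction. The stated rule makes the chosen model's cross-validated NDCG too high and RMSE too low on average, and inflates its gain over both baselines. This is a rule stated wrongly, not detail left to a fuller document.

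The absolute size is probably small: about 0.001 to 0.013 NDCG with 1000 users, on the assumed SD, correlation and 3 to 200 candidates. It shrinks further if the candidates differ clearly in true performance. A large gain over random recommendation would survive it. A small gain over the metadata-only baseline might not, since the optimism can approach the 0.0078 at which a nominal 5% comparison declares a gain. The separate sample of 200 does not settle that question, because no baseline is described there.

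**What to change.** Correct the count from 3 to 5, and replace the selection sentence for the phase 1 performance report with wording such as:

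> Within each of the 5 outer folds, feature set, architecture and hyperparameters are chosen on the validation users only, by one pre-named metric. Each outer test fold is scored once, and performance is averaged over all 5 test folds. The baselines are scored on the same test users, and the paired difference is reported with a user-level confidence interval.

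The choice must be made separately inside each outer fold. If one configuration is picked on validation scores pooled over rotations, users who serve as validation in one rotation and as test in another carry some of the optimism back in.

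Under Results, the article says participants had completed both surveys by June 2025 and that analysis is underway. The model that produced the phase 2 playlists has therefore presumably been chosen already, and this change can alter only the phase 1 performance estimates. If that model was chosen on test folds, the report should say so and label its phase 1 test score as optimistic.

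The cost is a few sentences, some added computing for the nested selection, and a slightly less favourable reported performance. No new data are needed.

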**Methods:**

Participants (N=1200) will be aged 55 years or older and residing in the United States. In phase 1, participants (n=1000) will receive 5 randomized songs and complete a survey to understand the sentiment, cultural relevance, and perceived benefit for each song. Brief, researcher-created Likert surveys will be used. In phase 2, survey data will be used to develop ML algorithms in collaboration with the University of Massachusetts Amherst Center for Data Science and Artificial Intelligence. These ML models will be integrated into the digital music intervention and tested with a separate sample of 200 participants. Similar to phase 1, participants will be provided with sets of songs generated by the recommendation system based on the target goal (ie, to reduce depression). The recommendation accuracy of the ML algorithm will be assessed using multiple performance metrics, including root-mean-square error and normalized discounted cumulative gain as well as the mean acceptability score with a goal of 85% user acceptability.

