## Discussion

### Principal Results

To our knowledge, this is the first digital singing intervention aimed at lifestyle factors associated with AD, such as depression, for those aged 55 years or older. It is important to improve intervention fit and cultural acceptability to ensure accessibility and usability for rural-residing older adults who may benefit the most from this type of intervention. While other music interventions are available, none are specifically aimed at managing symptoms of depression and cognitive reserve in cognitively healthy adults. Using ML to improve the existing intervention algorithms should improve music recommendations and engagement in end users. ML models should also allow the research team to better understand musical factors associated with sadness and depression symptoms, furthering knowledge on the most appropriate music interventions for mood symptoms in rural-residing older adults.

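### The two offline baselines cannot tell personalisation from learning which songs are liked on average, and SingFit's current algorithm is not a comparator

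*Protocol article*

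**What the plan says.** Methods, Phase 2: Machine Learning Model Implementation and Evaluation, names the comparators: "Baseline performance will be measured using a purely random recommendation system and a content-based learning-to-rank approach that relies solely on metadata features". Their purpose follows: "These baseline benchmarks will help gauge the added benefit of more complex neural network recommendation algorithms". The section splits the data by user in five-fold cross-validation, so that the test imitates cold start. It also plans to compare satisfaction scores between phases, and its Aim 3 paragraph seeks at least 80% accuracy in producing playlists tailored to the individual.

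Methods, Music Metadata, shows that a recommender is already in use: "Music metadata is used in SingFit’s current song recommendation algorithms and will be used in knowledge graphs". Popularity is among the listed metadata. The abstract says of the new models: "These ML models will be integrated into the digital music intervention and tested with a separate sample of 200 participants". The Discussion, Principal Results, states the expectation: "Using ML to improve the existing intervention algorithms should improve music recommendations and engagement in end users".

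On the phase 1 songs, Methods, Phase 1, says: "Participants will receive 5 songs randomly chosen from a set of songs based on age and musical arousal".

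**The concern.** A comparator set determines what a win can mean. Here two readings of a win are left open.

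First, personalisation. A held-out user has no ratings in the training data. Unless some of that user's own ratings are fed in, which the article does not describe, individual tailoring must come from user features such as demographics or the mood items. The main signal left in the ratings is how well each song is liked by everyone, or by an age cohort. A ranking built on that alone gives users the same order for the same songs, and neither named baseline represents it. A gain over both could therefore be reported as benefit of the neural model, or as individual tailoring, when a table of song averages would have done as well.

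Second, improvement on the product. The Discussion expects better recommendations than the existing algorithms give, but no planned offline comparison includes them.

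At stake is the interpretation of the model comparison and which model is worth deploying.

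**Working it through.** The plan gives no figure that depends on the choice of comparators, so there is none to reproduce. Three checks were made.

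**1. Can a non-personalised song average beat both baselines?**

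From the article: up to 1000 users with 5 rated songs each on a 5-point scale. Five folds by user leave 1000/5 = 200 test users and 800 others per fold.

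Assumed, because the article gives no values: 100 or 300 songs; mean rating 3.6; song SD 0.3 or 0.5; user SD 0.6; residual SD 0.9; metadata explaining 25%, 50% or 75% of the between-song variance. All 800 other users serve for training, which gives 800 × 5 / 100 = 40 or 800 × 5 / 300 ≈ 13 training ratings per song.

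Rankers, all applied to each test user's own five songs:
- Random order.
- Metadata-only: ridge regression of the rating on eight simulated song features, a simple stand-in for learning-to-rank.
- Song average: (sum of centred training ratings) / (n + λ), with λ = (0.6² + 0.9²) / song SD². No user information enters.

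NDCG = Σ rᵢ/log₂(i+1) in the ranked order, divided by the same sum in the ideal order. Cells show mean NDCG / mean rating of the top-ranked song, over 40 replicates.

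| Songs | Song SD | Metadata share | Random | Metadata-only | Song average |
|---|---|---|---|---|---|
| 100 | 0.3 | 25% | 0.935 / 3.54 | 0.947 / 3.72 | 0.953 / 3.82 |
| 100 | 0.3 | 75% | 0.936 / 3.54 | 0.954 / 3.82 | 0.954 / 3.82 |
| 100 | 0.5 | 25% | 0.931 / 3.54 | 0.950 / 3.82 | 0.963 / 4.02 |
| 100 | 0.5 | 75% | 0.931 / 3.54 | 0.960 / 3.98 | 0.962 / 4.01 |
| 300 | 0.3 | 25% | 0.936 / 3.54 | 0.946 / 3.70 | 0.950 / 3.77 |
| 300 | 0.3 | 75% | 0.936 / 3.56 | 0.953 / 3.83 | 0.949 / 3.76 |
| 300 | 0.5 | 25% | 0.932 / 3.55 | 0.949 / 3.80 | 0.961 / 3.99 |
| 300 | 0.5 | 75% | 0.932 / 3.54 | 0.960 / 3.97 | 0.959 / 3.95 |

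At a 50% share the song average equalled or exceeded the metadata ranker in all four settings. Against random, the song average gained about 0.01 to 0.03 in NDCG and 0.2 to 0.5 points on the top song. Against metadata-only, the top song was rated up to 4.02 − 3.82 = 0.20 points higher. It fell behind only with 300 songs and a 75% metadata share (3.76 − 3.83 = −0.07 and 3.95 − 3.97 = −0.02).

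**2. Does beating random imply beating the current algorithm?**

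No. With assumed mean ratings of 3.0 (random), 3.4 (new model) and 3.6 (current algorithm), the new model gains 3.4 − 3.0 = 0.4 over random and loses 3.6 − 3.4 = 0.2 to the current algorithm.

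**3. Does the comparison across phases fill the gap?**

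With 1000 and 200 participants, the article's planning SD of 1.2, two-sided 5% and 80% power, the detectable difference is (1.960 + 0.842) × 1.2 × √(1/1000 + 1/200) = 2.802 × 1.2 × 0.0775 ≈ 0.26 points. Size is therefore not its main limit. The samples are separate and not randomised against each other, and the reference is songs drawn at random within an age and arousal filter, which the article does not present as the current algorithm.

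**The case against.** The case for the plan has five parts.

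- *The baselines have a narrower purpose.* They are meant to gauge what neural complexity adds. No aim claims superiority over the current algorithm, and the Aim 3 targets are absolute. This stands: a reader might infer that the study sets out to prove the product is improved, but the source is one forward-looking sentence in the Discussion. The song-average gap remains, because it bears directly on the narrower purpose.
- *The metadata ranker can use popularity and resembles the current algorithm.* Partly right. Popularity is a listed tag, but the article does not say that it is the phase 1 average, and it does not equate this ranker with the algorithm in use. It is at most a partial stand-in.
- *The random baseline is fair.* A reader might infer from its description that it ignores the age and arousal rules, so that the model would be credited with age matching. The article does not support this. It leaves the candidate pool undefined, and in the offline test only a user's five rated songs carry labels. These have already passed the age and arousal filter, so ordering them at random stays within it.
- *The phases are also compared, and phase 1 follows SingFit's own practice.* True in part: "SingFit’s music selections are chosen from participants’ adolescence and young adulthood to ensure familiarity and narrative memory associations with the music". The comparison is relevant but indirect.
- *An article condenses the benchmark list.* Possible, but this article names its two baselines and what they are to show, so the list can be judged against that purpose.

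**Conclusion.** The concern holds in a limited form. The two named baselines cannot separate personalisation, or benefit specific to the neural model, from knowledge of which songs are well liked on average. In the simulation a ranker with no personalisation cleared the random baseline throughout and matched or beat the metadata-only ranker in most settings. Those sizes rest on assumed song numbers, variances and metadata strength, and on a simple metadata ranker, so they show that the misreading is possible, not how large it will be. The omission of SingFit's current algorithm is a fact of the text. It means that the Discussion's expectation of improvement has no direct test; it does not mean that the new model is no better. No stated sample size, power figure or acceptability target changes.

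**What to change.** In the Phase 2 methods section:

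1. Add a non-personalised song-average ranking, overall or within age band, estimated in the training users of each fold only and scored on the same held-out users. Claim added benefit of the neural model, or personalisation, only if the model beats it.
2. Where the current SingFit algorithm can score the same held-out songs, add it as a benchmark. Where it cannot, limit the statement in Principal Results to the baselines actually tested.

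The first change is a re-scoring of data already held, and analysis was still under way when the article was written. The second depends on whether the current algorithm can rank survey songs for users without history; the article does not describe its inputs. The price is a little more analysis, and a reported gain that may look smaller.
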